## Abstract

**Background:**

Orthokeratology is a nonsurgical corneal reshaping technique used for the temporary correction of myopia and for myopia control. Nighttime use induces central epithelial thinning and midperipheral thickening, altering corneal asphericity and higher-order aberrations.

**Objective:**

The primary objective is to determine the change in anterior corneal spherical aberration after 1 month of orthokeratology use. Secondary objectives include evaluating changes in total corneal refractive power, the Q value, and epithelial thickness.

**Methods:**

This prospective quasi-experimental pre-post study was conducted at a private ophthalmology clinic (Licari Vision Clinic, Tarragona, Spain). Participants were patients aged 8 to 21 years with myopia ranging from −1.00 to −5.00 D who underwent nighttime orthokeratology for 1 month. Outcome measurements included Pentacam tomography, anterior segment optical coherence tomography (OCT), and Zernike analysis, all performed in the morning 1 to 3 hours after lens removal. Cycloplegic refraction was performed at baseline only to confirm eligibility criteria and inform orthokeratology lens design. A minimum of 23 participants was required to detect a change of ≥0.14 μm in anterior corneal spherical aberration (α=.05; β=.05; power=95%; SD 0.166 μm), incorporating a 20% dropout rate. The unit of analysis will be the eye, including both eyes of each participant. To account for the nonindependence of contralateral eyes in the same participant’s within-subject repeated measurements, the primary and secondary outcomes will be analyzed using linear mixed-effects models with a fixed effect for time (baseline vs 1 month) and a random intercept for each participant. A significance level of *P*<.05 will be applied in all cases.

**Results:**

The protocol received a favorable ethics opinion from the Drug Research Ethics Committee (*Comité de Ética de la Investigación con medicamentos* [CEIm]) of the Pere Virgili Institute for Health Research (*Institut d'Investigació Sanitària Pere Virgili* [IISPV]) in October 2024 (CEIm Code 159/2024) and was registered at ClinicalTrials.gov (NCT06775509). This study received no external funding. Recruitment was completed. Data collection has been finalized, and data analysis is currently underway. The study findings are expected to be published in January 2027.

**Conclusions:**

Corneal optical quality may be modified after 1 month of orthokeratology lens use, and the findings may contribute to refining clinical decision-making regarding the use of orthokeratology for myopia management.

## Introduction

The cornea is the eye’s transparent, avascular tissue, comprising 5 distinct layers: the corneal epithelium, Bowman membrane, the stroma, Descemet membrane, and the endothelium. Its thickness varies, being thinner centrally (approximately 0.52 mm) and reaching nearly 1 mm near the limbus. The outermost layer, the corneal epithelium, is vital not only for protection but also for making a significant contribution to corneal refractive power.

The human cornea is naturally prolate, with a steeper center and a flatter periphery, reflected by a mean Q value of approximately −0.27. This asphericity minimizes spherical aberration under physiological conditions; in contrast, oblate corneas (Q>0), which are steeper in the periphery, exacerbate spherical aberrations.

Orthokeratology is a clinical technique that temporarily reshapes the cornea to eliminate or reduce refractive error [1]. Orthokeratology lenses are typically worn overnight (overnight orthokeratology) and removed upon waking, allowing patients to achieve clear vision without correction throughout the day. These lenses are made of rigid gas-permeable (RGP) material and are designed to reduce myopia by flattening the central cornea [2]. This treatment is reversible, safe, and approved by the US Food and Drug Administration (FDA). Although myopia correction and control are the most widely studied applications of orthokeratology, lens designs for the correction of hyperopia and astigmatism have also been developed and reported in the literature, broadening the clinical scope of this technique.

Although orthokeratology effectively reduces myopia [3] and enables good uncorrected vision during the day, numerous studies have demonstrated that the combination of central corneal flattening and midperipheral corneal thickening leads to a significant increase in higher-order aberrations (HOAs), resulting in decreased visual quality [4,5].

With the use of orthokeratology, higher-order corneal aberrations increase significantly, particularly spherical aberration [6], and these increases correlate with the degree of myopic correction [7,8]. Several studies have concluded that the loss of optical quality is most evident within the first month but is not significant in subsequent months. Following short-term corneal remodeling, optical quality decreases to some extent, but the loss is considered acceptable [9-11].

As previously mentioned, orthokeratology causes central corneal epithelial thinning and midperipheral epithelial thickening [12]. Changes in epithelial thickness exhibit a nonuniform pattern, with greater thinning in the temporal and inferior regions than in the nasal and superior regions of the paracentral area and more pronounced thickening in the nasal region than in the temporal region of the midperiphery [12,13].

Despite the growing body of evidence on the optical effects of orthokeratology, previous studies have consistently reported that the optical deterioration induced by orthokeratology is fully established after 1 month of treatment, with no significant further changes observed thereafter. For this reason, the 1-month time point was selected to capture the maximum expected optical deterioration, as described in the literature. However, most of the previous evidence has been derived from analyses limited to the anterior corneal surface. This study aims to confirm whether these previously reported changes are also present when the whole cornea is systematically evaluated, including total corneal refractive power (TCRP) and total corneal aberrations derived from both the anterior and posterior surfaces, and to confirm the expected epithelial redistribution pattern, characterized by central thinning and midperipheral thickening. Accordingly, this study aims to determine the change in anterior corneal spherical aberration after 1 month of overnight orthokeratology use as its primary objective, with secondary objectives including the evaluation of changes in TCRP, Q value, and epithelial thickness.

## Methods

### Study Objectives

The primary objective of this study is to determine the change in anterior corneal spherical aberration, defined as the Zernike coefficient z(4,0) measured at a 7-mm pupil diameter, after 1 month of overnight orthokeratology.

The secondary objectives are to analyze changes in refractive maps obtained using the Pentacam topographic system (OCULUS Optikgeräte GmbH), including TCRP and corneal asphericity; to assess corneal aberrations through Zernike analysis at the remaining pupil diameters, examining the relationship between changes in anterior corneal asphericity and induced spherical aberration; and to evaluate changes in central and peripheral epithelial thickness using corneal optical coherence tomography (OCT) and their correlation with changes in corneal asphericity and induced aberrations.

For clarity, the primary outcome of the study is the change in anterior corneal spherical aberration z(4,0) at a 7-mm pupil diameter, from baseline to the 1-month follow-up visit. All remaining measures constitute secondary outcomes, namely, anterior corneal spherical aberration z(4,0) at 3-mm and 5-mm pupil diameters; spherical-like, coma, coma-like, third-order root mean square (RMS), fourth-order RMS, and total HOA RMS at all 3 pupil diameters; TCRP at 3, 5, and 7 mm; corneal asphericity (Q value); and central and peripheral epithelial thickness. Axial length is reported for descriptive purposes only and does not constitute an outcome measure.

Cycloplegic refraction was performed at the baseline visit only, to confirm the degree of myopia for eligibility assessment and, together with corneal topography, to inform the orthokeratology lens design. It was not repeated at follow-up visits and was not used as a correlational variable in the analysis of posttreatment corneal changes.

### Study Design and Setting

This was a prospective, quasi-experimental, pre-post study. Data were collected at baseline and 1 month after the commencement of the intervention. The study was conducted at the Licari Vision Clinic in Tarragona, Spain. Potential participants and their guardians were fully informed of the study procedures, and informed consent or assent was obtained prior to screening.

### Participant Selection

Textbox 1 shows the inclusion and exclusion criteria for this study.

Textbox 1.Inclusion and exclusion criteria.Lens centration is assessed at the first follow-up visit after the first night of lens wear and serves as a continuation criterion. All other inclusion criteria are assessed during screening.

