**Inclusion criteria**
Age 8 to 21 years and willingness to participate in the studyUse of orthokeratology lenses for 8 to 10 hours per night after being informed about the risks and benefits of the treatmentSpherical myopic refractive error between −1.00 and −5.00 diopters (D), with following-the-rule astigmatism of ≤1.50 DBest-corrected distance visual acuity of 20/20 or better before treatmentOrthokeratology lens centration or radial lens decentration of <0.5 mm, as determined by slit-lamp examination

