#### Lens Fitting Criteria

Paragon CRT orthokeratology lenses were fitted by the principal investigator following standard orthokeratology fitting procedures. Lens fit was assessed by evaluating the fluorescein pattern under slit-lamp examination to confirm adequate central support, midperipheral alignment, and peripheral clearance. Treatment centration was assessed at each follow-up visit using 2 complementary methods: slit-lamp evaluation of the fluorescein pattern and topographic analysis of the treatment zone using axial and tangential maps obtained with the Pentacam system, which allowed objective verification of the treatment zone centration relative to the corneal apex. Participants exhibiting radial decentration greater than 0.5 mm were excluded from the study.

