#### Discontinuation Criteria

Participants were excluded from the study if any of the following situations occurred: lens decentration greater than 0.5 mm radially, eye infection, lens intolerance, any adverse ocular event, or voluntary withdrawal from the study at any time.

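### The decentration rule leaves two cases unsettled and lets a 1-month Pentacam finding remove participants who completed treatment

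*Protocol article*

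**What the plan says.** The protocol article states the rule in three places.

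- **Participant Selection, Textbox 1.** On timing: "Lens centration is assessed at the first follow-up visit after the first night of lens wear and serves as a continuation criterion". The inclusion criterion itself is centration or "radial lens decentration of <0.5 mm, as determined by slit-lamp examination".
- **Lens Fitting Criteria.** "Treatment centration was assessed at each follow-up visit using 2 complementary methods". These are the slit-lamp fluorescein pattern and Pentacam maps of the treatment zone, "which allowed objective verification of the treatment zone centration relative to the corneal apex". The paragraph ends: "Participants exhibiting radial decentration greater than 0.5 mm were excluded from the study".
- **Discontinuation Criteria.** The reasons for leaving the study include "lens decentration greater than 0.5 mm radially, eye infection, lens intolerance, any adverse ocular event, or voluntary withdrawal". No visit or method is attached to decentration here.

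Data Recording and Storage lists the follow-up visits as 1 night, 1 week and 1 month, each with Pentacam topography. Study Objectives makes the primary outcome the change in z(4,0) at 7 mm from baseline to 1 month, and Ocular Variables takes the Zernike coefficients from the Pentacam. Results says that data collection is finished and analysis has begun.

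**The concern.** A rule that decides who stays in a single-arm pre-post study should give one answer for each participant, and preferably one that does not depend on how the cornea responded. The three statements differ on the boundary, on the object measured and on the method.

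The larger issue is timing relative to the outcome. A check after the first night is settled before any 1-month outcome exists. A check at 1 month rests on a map from the instrument and visit that supply z(4,0). Removing a participant at that point selects the sample on the corneal response to treatment, so the estimated mean change would describe well-centred responders rather than everyone treated for a month. With data collection over, unsettled wording also leaves the set of participants open to being decided after outcomes have been seen.

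**Working it through.** **The plan's own figure.** Sample Size gives a two-sided α of 0.05, power of 95%, SD 0.166 μm and a difference of 0.14 μm. For a mean paired change, n = ((1.960 + 1.645) × 0.166 / 0.14)² = 18.27, rounded up to 19. Dividing the unrounded value by 1 − 0.20 gives 22.84, rounded up to 23. Both stated figures reproduce and are not in question. The margin for all losses together is 23 − 19 = 4 participants.

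**The statements side by side.**

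| Place | Object | Method | Visit | Boundary |
|---|---|---|---|---|
| Textbox 1 | lens | slit lamp | after night 1 | below 0.5 mm continues |
| Lens Fitting Criteria | treatment centration, including the zone relative to the apex | slit lamp and Pentacam maps | every follow-up visit | above 0.5 mm excluded |
| Discontinuation Criteria | lens | not named | not named | above 0.5 mm excluded |

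**Test cases.**

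1. *Exactly 0.5 mm.* Fails Textbox 1, but is not excluded by either of the other two sections. Unresolved.
2. *Lens below 0.5 mm by slit lamp, treatment zone above 0.5 mm on the map.* Meets Textbox 1 and, as far as the lens goes, is not caught by Discontinuation Criteria. It can be excluded under Lens Fitting Criteria. No tie-break is given. Unresolved.
3. *Centred after night 1, above 0.5 mm at 1 week or 1 month.* Passes the entry check and is later caught by the exclusion rule. This is coherent if the two are sequential stages.
4. *As case 3, but found only on the 1-month map.* The participant has completed the treatment period and has a 1-month z(4,0). Lens Fitting Criteria would still exclude them, on the same visit's Pentacam examination.

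**Possible size.** Let p be the proportion removed after completing, and D the difference in mean change between those kept and those removed. Then mean(kept) − mean(all) = p × D. The article gives neither p nor D. As an assumption, take all 23 as otherwise complete, removals from 1 to 4 (the loss margin), and D from 0 up to the plan's reference value of 0.14 μm:

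- 1 removed: p = 1/23 = 4.3%; shift from 0 to 0.043 × 0.14 = 0.006 μm.
- 4 removed: p = 4/23 = 17.4%; shift from 0 to 0.174 × 0.14 = 0.024 μm.

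The direction is unknown. These are illustrations, not estimates of how many participants were affected.

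**The case against.** The strongest reply is that this is ordinary structure. An entry criterion is followed by discontinuation criteria, and passing the first protects nobody from the second. That stands. A reader might infer from Textbox 1 that centration is judged once only, so that later removal contradicts it. Textbox 1 does not say so, and the visit difference alone is not an error.

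The two methods are called complementary, and the map can be seen as confirming the slit-lamp finding. That is fair, and a condensed article may leave a tie-break to the full protocol. But the inclusion criterion is tied to one method ("as determined by slit-lamp examination") and the fitting section to two, with an exclusion following directly. The published text therefore gives no single rule. The boundary mismatch is real but touches only one value.

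The exclusions are from the study. Only the adherence rule speaks of exclusion from the analysis, so the effect of decentration on the analysis set is implied rather than stated. This also stands, and it is one more thing for the text to settle. The planned mixed model under missing at random does not dispose of it: the model contains only time and a participant intercept, so a 1-month value withheld because of a 1-month map is not explained by anything in the model.

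Three other inferences go too far. Removal by participant while the eye is the unit of analysis is a design choice, worded consistently in both exclusion passages, and not a contradiction. Nothing shows that the set was in fact chosen with outcomes in view; the text only leaves that possible. Finally, the article does not say that coma responds to decentration. Repeating the coma outcomes is a precaution based on optical reasoning, not a documented effect.

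**Conclusion.** The concern holds in a limited form. The rule is inconsistent at exactly 0.5 mm and silent on whether lens or treatment zone governs when they disagree. The more consequential problem lies within Lens Fitting Criteria and needs no conflict with Textbox 1: read as written, it allows removal at 1 month on the examination that yields the primary outcome, and no planned analysis shows the effect.

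This reading assumes that the exclusion sentence applies at every visit named just before it, and that excluded participants also leave the analysis; the article confirms neither outright. The number affected is unknown. Under the assumptions shown, the shift in the primary estimate would be at most 0.024 μm against a reference of 0.14 μm. That is modest for the primary outcome, but worth showing because the check is cheap. No view is taken on which threshold, method or visit is clinically right.

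**What to change.** 1. Reconcile Participant Selection (with its inclusion criterion), Lens Fitting Criteria and Discontinuation Criteria into one statement of quantity, method, visit and boundary value, and say whether an exclusion from the study is also an exclusion from the analysis. The choice is the investigator's. Date the statement before the outcome analysis; since analysis has begun, state what had been seen by then.
2. Report how many participants and eyes were removed for decentration, at which visit and by which method.
3. Repeat the primary model, and the models for the coma outcomes, in all participants who met the night-1 criterion and have 1-month data, whatever their later decentration. Show this beside the main result.

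Participants removed before 1 month may have no outcome data; they can be counted but not analysed, so the repeat analysis addresses only removals at the final visit. The cost is a text correction, one table and one further model run on stored data. The downside is a less firm conclusion if the two results differ.

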**Inclusion criteria**
Age 8 to 21 years and willingness to participate in the studyUse of orthokeratology lenses for 8 to 10 hours per night after being informed about the risks and benefits of the treatmentSpherical myopic refractive error between −1.00 and −5.00 diopters (D), with following-the-rule astigmatism of ≤1.50 DBest-corrected distance visual acuity of 20/20 or better before treatmentOrthokeratology lens centration or radial lens decentration of <0.5 mm, as determined by slit-lamp examination
**Exclusion criteria**
History of rigid contact lens use or ocular or systemic contraindications to orthokeratology identified during routine examinationPrevious refractive modulation procedure of any typeCorneal pathology, dry eye disease, glaucoma, retinal pathology, strabismus, ptosis, amblyopia, or a history of ocular allergy or infection

### Data Recording and Storage

Upon enrollment, each participant received a study identification number. Baseline examinations were conducted prior to the initiation of orthokeratology lens wear. The baseline protocol comprised objective refraction under cycloplegia, axial length measurement, comprehensive topographic analysis with the Pentacam system, epithelial thickness analysis, pupil diameter measurement, and orthokeratology lens fitting.

Cycloplegic refraction was performed using 1% cyclopentolate hydrochloride (2 drops instilled 5 minutes apart). Refraction was measured 45 minutes after the first drop using a combination of autorefractometry, retinoscopy, and subjective refraction to the maximum plus for maximum visual acuity (MPMVA).

Axial length was measured with the MYAH myopia management system (Topcon) as part of the routine baseline clinical characterization of participants. Axial length data were collected for descriptive purposes only and do not form part of the primary or secondary objectives of the study.

Epithelial thickness was analyzed using the REVO SOCT 27 anterior segment OCT (Optopol Technology; 27,000 A-scans/second). Corneal epithelial thickness maps were obtained automatically using the device’s integrated segmentation software, without manual intervention by the investigator.

Paragon CRT orthokeratology lenses (Paragon Vision Sciences) were used for all participants. The investigator performed lens fitting and evaluated the fit using fluorescein.

At each follow-up visit after the start of orthokeratology lens use, a complete contact lens assessment was performed. All follow-up measurements were performed in the morning, between 1 and 3 hours after lens removal, to ensure consistency across visits and minimize the effect of corneal recovery over time. Each visit comprised slit-lamp examination to evaluate ocular surface integrity and lens fit, visual acuity assessment, corneal topography with the Pentacam system, and epithelial thickness analysis using the REVO SOCT 27 anterior segment OCT (27,000 A-scans/second) to evaluate the corneal response to orthokeratology lens wear. Epithelial thickness maps were obtained automatically using the device’s integrated segmentation software, without manual intervention by the investigator.

Follow-up visits were conducted by the investigator after 1 night, 1 week, and 1 month of lens wear.

### Sample Size

The sample size was determined based on changes in anterior corneal spherical aberration (Zernike coefficient z[4,0], expressed in microns), as it is one of the HOAs most strongly associated with optical quality after orthokeratology. The threshold of 0.14 μm was derived from the Rayleigh criterion (λ/4) and was used as an optical reference value for sample size estimation, rather than as a validated clinical threshold for visual quality. This criterion establishes that an increase in spherical aberration exceeding one quarter of the wavelength of light deteriorates optical quality.

Using a reference wavelength (λ) of 0.555 μm (peak sensitivity of the human visual system), this yields a threshold of 0.555/4≈0.14 μm.

With a 2-sided α of 0.05 (type I error) and a β of 0.05 (type II error), corresponding to a statistical power of 95%, and an assumed SD of 0.166 μm, a minimum of 19 participants was required. Considering a 20% loss to follow-up rate, a total of 23 participants were recruited.

The sample size was calculated using GRANMO (version 8; Municipal Institute of Medical Research) [14].

This calculation was based exclusively on the primary outcome (anterior corneal spherical aberration).

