The specific aberrations analyzed are the fourth-order spherical aberration z(4,0), expressed in microns; the spherical-like aberration of orders 4 and 6, represented by its RMS and calculated as the square root of the sum of the squares of z(4,0) and z(6,0), expressed in microns; the third-order coma aberration, represented by its RMS and expressed in microns as the square root of the sum of the squares of z(3,−1) and z(1,3); the coma-like aberration of orders 3 and 5, represented by its RMS expressed in microns as the square root of the sum of the squares of z(3,−1), z(1,3), z(5,−1), and z(1,5); the third-order RMS aberration, expressed in microns as the square root of the sum of the squares of z(3,−3), z(3,−1), z(1,3), and z(3,3); the fourth-order RMS aberration, represented in microns as the square root of the sum of the squares of z(4,−4), z(4,−2), z(4,0), z(2,4), and z(4,4); and the total HOA RMS from the third to the sixth order, represented in microns as the square root of the sum of the squares of all Zernike coefficients from orders 3, 4, 5, and 6.

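### The 0.14 μm planning change is presented as the quarter-wave limit for z(4,0), but without conversion to the coefficient scale it is about 3.4 times that limit (1.5 times if the coefficients are unnormalised)

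*Protocol article*

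**What the plan says.** The Sample Size section of the protocol article bases the calculation on the change in anterior corneal z(4,0), in microns. It names the Rayleigh quarter-wavelength criterion as the origin of the threshold, takes 0.555 μm as the reference wavelength, and concludes that "this yields a threshold of 0.555/4≈0.14 μm". It explains the criterion in one sentence: "This criterion establishes that an increase in spherical aberration exceeding one quarter of the wavelength of light deteriorates optical quality". It does not say whether the quarter wavelength is peak-to-valley or RMS, and it shows no step from wavefront error to coefficient.

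The same section calls 0.14 μm an optical reference value for sizing the study and says that it is not a validated clinical threshold. With two-sided α 0.05, power 95% and "an assumed SD of 0.166 μm", it arrives at 19 participants, raised to 23 for loss to follow-up.

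The scale of the coefficients has to be read from the Ocular Variables section. There the spherical-like aberration is "represented by its RMS and calculated as the square root of the sum of the squares of z(4,0) and z(6,0"), and the other RMS measures are built in the same way.

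**The concern.** A quarter-wave limit on peak-to-valley error and a Zernike coefficient can both be given in microns, but they are different quantities. The first is the largest path difference across the pupil. The second multiplies a polynomial whose range across the pupil is greater than 1. Carrying the number from one to the other unchanged makes the planning change larger than the optical limit that it is said to represent.

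What is at stake is the justification of the effect size. A reader would take the study to have 95% power for a change at the quarter-wave limit, and the same derivation could be carried into the results paper. The calculation for 0.14 μm itself is not in question.

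**Working it through.** **Inputs.** From the Sample Size section: λ = 0.555 μm, change 0.14 μm, SD 0.166 μm, two-sided α 0.05, power 95%, 19 evaluable and 23 recruited. From Ocular Variables: RMS is the root of the summed squared coefficients. Two premises are not written in the protocol:

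- The quarter-wave criterion is a peak-to-valley limit (its standard meaning).
- The coefficients are RMS-normalised (inferred from the RMS formulas).

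**1. The plan's own figure.** Reading 0.166 μm as the SD of the paired change:

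n = [SD × (z₀.₉₇₅ + z₀.₉₅) / change]² = [0.166 × (1.960 + 1.645) / 0.14]² = 18.27, rounded up to 19.

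This reproduces the plan. A one-sided version gives 16 and a two-sample version 37 per group, so the paired two-sided formula is the one used. The exact t calculation gives 21.

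**2. The coefficient scale.** The RMS-normalised term is Z(r) = √5 (6r⁴ − 6r² + 1) for r from 0 to 1.

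- RMS: with u = r², the integral of (6u² − 6u + 1)² over 0 to 1 is 1/5. Times 5 this is 1, so a coefficient of 1 μm has an RMS of 1 μm. Root-sum-of-squares formulas need exactly this property.
- Peak to valley: the bracket is 1 at r = 0 and r = 1, and −0.5 at r² = 0.5. Its range is 1.5, so the term's range is 1.5 × √5 = 3.354.

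Without the √5 the range is 1.5, but the RMS per unit coefficient is 1/√5 = 0.447. The formulas under Ocular Variables would then not give RMS values. That is why RMS normalisation is the likelier reading.

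**3. Conversion.** The quarter wave is 0.555/4 = 0.13875 μm.

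| Reading | Quarter-wave limit in z(4,0) | 0.14 μm relative to it |
|---|---|---|
| Peak-to-valley, RMS-normalised | 0.13875/3.354 = 0.0414 μm | 3.38 |
| Peak-to-valley, unnormalised | 0.13875/1.5 = 0.0925 μm | 1.51 |
| Limit applied to the coefficient itself (as the plan does) | 0.13875 μm | 1.01 |

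In the other direction, 0.14 μm in an RMS-normalised z(4,0) is 0.14 × 3.354 = 0.470 μm peak to valley, and 0.470/0.555 = 0.85 wavelength, against 0.25 for the criterion.

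**4. Power at the converted limits.** Two-sided paired t test (noncentral t), SD 0.166 μm, one change per participant:

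| True change | n = 19 | n = 23 |
|---|---|---|
| 0.0414 μm | 18% | 21% |
| 0.0925 μm | 63% | 72% |
| 0.14 μm | 93.5% | 97% |

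The last row falls slightly short of 95% at n = 19 because the plan's 19 comes from the normal approximation. That is not part of this point.

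**The case against.** The strongest reply is that the protocol never says peak-to-valley. It speaks of spherical aberration exceeding a quarter wavelength, and taken literally as a limit on the coefficient this needs no conversion (third row of the conversion table). There is no contradiction within the document until the standard definition is supplied. This stands as a limit on certainty. But the protocol names the Rayleigh criterion as its source, and under the usual meaning of that criterion the derivation fails on either scaling. The factor of 3.4 is likewise inferred, since the device's normalisation is not stated.

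A second reply is that 0.14 μm is only a reference value. That caveat disclaims clinical validation. It does not disclaim the optical derivation, which the following sentences set out and compute.

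Three stronger readings are tempting, and the documents do not support them.

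- A reader might infer that the study is underpowered. The planned analysis tests the time effect against no change, and the protocol does not set 0.041 μm as a target. If the true change is 0.14 μm or more, the power of that test is not affected by where the number came from.
- A reader might infer that a mean change of 0.05 to 0.13 μm will be judged to lie below the optical limit. The Statistical Analysis section has no such rule. It reports mean differences with 95% CIs and never compares them with 0.14 μm.
- A reader might infer that the primary CI should be read against 0.041 μm. That would add a threshold after data collection has ended. The criterion also concerns error across a whole wavefront, whereas the outcome is a change in one anterior-surface term, so rescaling would not make it a suitable margin.

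**Conclusion.** The concern holds as a fault in the justification of the effect size. Under the standard peak-to-valley meaning of the named criterion, 0.14 μm is not the quarter-wave limit for z(4,0): it is about 3.4 times that limit if the coefficients are RMS-normalised, as the protocol's RMS formulas imply, and about 1.5 times if they are not. The 95% power belongs to a 0.14 μm change and not to the optical criterion cited.

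The division 0.555/4 is right, the sample size follows from its inputs, and no planned estimate, test or interval changes. The conclusion rests on the peak-to-valley definition, which the protocol does not state. The size of the factor rests on the normalisation, and the power figures on reading 0.166 μm as the SD of the paired change.

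**What to change.** In the Sample Size section, state that 0.14 μm is an assumed change used for planning, and remove the statement that it is the quarter-wave limit for z(4,0).

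If the authors wish to keep an optical reference, they should first confirm how the Pentacam normalises its coefficients. They should then give the reference in coefficient units (about 0.041 μm if RMS-normalised, about 0.093 μm if not) and state the lower power that goes with it. The results paper should not describe a mean change below 0.14 μm as below the Rayleigh limit.

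No formal margin should be added for the primary CI, and the sample size should stay as it is. The cost is rewording one paragraph while the analysis is under way. The downside is that, if the optical criterion is kept, the study states less favourable power for it.
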